## ***Patients and methods***

### **Study sample**

The study sample will be composed of 1800 patients, evenly distributed over the three study arms. Sample size is based on an expected response rate (for the questionnaire) of 75%. We will include patients who undergo surgery or biopsy (1600 patients) or blood drawing (200 patients). The former category of patients will contain patients who have a skin condition, a colorectal condition or a condition in the head/neck area. We include patients with malignant and non-malignant conditions of the same tissues or organs with a ratio of about 3:2, dependent on availability in each hospital. The absolute number of patients with specific conditions will also depend on the availability of these patients in the four hospitals. In the VUmc we will not include patients with (malignant and benign) colorectal conditions and malignant head/neck conditions, because almost all of them will also be asked to participate in a biobank (String of Pearls Initiative), which might confuse patients about what they are asked to give consent for. In the NKI-AVL, only patients with malignant conditions will be included. Figure 1 gives an overview of the number of patients in each of the groups in the four hospitals.

We will include patients between the ages of 18 and 80 years. There are two reasons for the upper age limit. First, we have learned from experience that patients over 80 are much less likely to be able or willing to complete questionnaires. Second, and more importantly, the two community hospitals in our study treat more patients over 80 than the two academic hospitals. Including these patients would mean that it would be difficult to determine whether any differences observed between patients from these different types of hospitals should be attributed to age differences or other causes.

Patients should be able to speak and read Dutch and have a sufficient mental capacity to complete the questionnaires by themselves. Patients will be included in the study by their treating physician or nurse practitioner.

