### ***Sample size, statistical power***

Sample size is based on an expected response of 75%, allowing sufficient power to address the major outcomes, i.e. consent rates and preferences for procedures, in different subgroups of e.g. hospitals, age and gender. In order to test the hypothesis that the two interventions result in a difference of at least 10% in consent rates, 0.1% non-consent in the opt-out plus or opt-out group versus 10% in the informed consent group, 121 patients per group are needed (80% power and a 2-sided alpha of 0.05; with continuity correction). The difference of 10% is based on our earlier research and the difference is considered a relevant loss of patient materials for research which may lead to selection bias. Because the setting of diagnosis and treatment is different between surgical and outpatient settings and also between general and academic hospitals, it is important to be able to compare the responses in these subgroups. We have also shown in our earlier studies that educational level is associated with preference for a certain procedure and this may also drive response rates of patients. Therefore we propose to include in each intervention group up to 600 patients to be able to conduct subgroup analysis and include adjustment factors; with a response rate of 75% and hence with 450 participants per group we could stratify for 3 to 4 factors, i.e. 90-150 per subgroup, and still have enough power to investigate a difference in response rate of 0.1% versus 10%. Patients will not be stratified by education or sex; we expect these two factors to be equally distributed across groups.

Another reason to obtain a large sample size is that the percentage of non-consenters is small, while it is important to assess their opinions and reasons for non-consent. In the earlier intervention study, 4.6% of respondents indicated in the questionnaire that they wanted to withhold consent or that they did not know whether they wanted to. A sample size of 1800 patients and a response rate of 75% will lead to approximately 62 patients who want to withhold consent or are not sure which choice to make.

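### The 121 per group does not follow from the printed inputs (0.1% vs 10% gives 95), and the subgroup sizes called sufficient start below 121

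*Protocol*

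**What the plan says.** Protocol, Sample size, statistical power. The aim is to test whether "the two interventions result in a difference of at least 10% in consent rates". The requirement is given as "0.1% non-consent in the opt-out plus or opt-out group versus 10% in the informed consent group, 121 patients per group are needed", under "80% power and a 2-sided alpha of 0.05; with continuity correction".

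The section then enlarges each arm to as many as 600 so that subgroups can be analysed and adjustment factors included. After allowing for 75% response, it says that "with 450 participants per group we could stratify for 3 to 4 factors, i.e. 90-150 per subgroup, and still have enough power" for a difference of 0.1% versus 10%. That sentence calls the outcome a response rate. Because the two percentages are the same, I read it as the same consent contrast.

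Protocol, Study sample: the 1800 patients are "evenly distributed over the three study arms", so each pairwise comparison is 1:1.

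**The concern.** Every input needed for the calculation is printed, so 121 can be checked, and it does not come out. There is also a conflict that needs no calculation: one sentence requires 121 per group for a contrast, and a later one accepts as few as 90 per subgroup for it.

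What is at stake is the subgroup statement. Subgroup analysis is a main stated reason for going from 121 to 600 per arm. If the rate behind the calculation was really higher than 0.1%, subgroups at the lower end of the range have clearly less than 80% power, and a null result there could be read with more confidence than it deserves.

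**Working it through.** **Inputs** (Protocol, Sample size, statistical power; allocation from Study sample): p1 = 0.001, p2 = 0.10, two-sided alpha 0.05 (z = 1.960), 80% power (z = 0.842), 1:1 allocation, continuity correction.

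**Formula** (pooled variance under the null, Fleiss continuity correction), with d = p2 − p1 and p̄ = (p1 + p2)/2:

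- n0 = [z_α √(2p̄(1 − p̄)) + z_β √(p1(1 − p1) + p2(1 − p2))]² / d²
- n = (n0/4) × [1 + √(1 + 4/(n0 d))]²

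**Attempt to reproduce 121 from the printed inputs**

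- d = 0.099 and p̄ = 0.0505, so 2p̄(1 − p̄) = 0.0959 and p1(1 − p1) + p2(1 − p2) = 0.0910.
- n0 = (1.960 × √0.0959 + 0.842 × √0.0910)² / 0.099² = (0.607 + 0.254)² / 0.0098 = 75.6
- n = (75.6/4) × [1 + √(1 + 4/(75.6 × 0.099))]² = 94.7, so **95 per group**

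Other standard versions at the same rates, alpha and 80% power do not reach 121 either:

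| Version | With correction | Without |
|---|---|---|
| Pooled, two-sided | 95 | 76 |
| Unpooled, two-sided | 92 | 73 |
| Pooled, one-sided | 79 | 60 |
| Arcsine, two-sided | 65 | 47 |

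**Single changes that do give 121** (same formula, with correction)

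| Change | n before rounding up | n |
|---|---|---|
| 1% instead of 0.1% | 120.7 | 121 |
| 90% instead of 80% power | 120.1 | 121 |
| alpha 0.0167 (0.05/3) instead of 0.05 | 120.4 | 121 |

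**Where 90 to 150 comes from.** 450/5 = 90, 450/4 = 112.5 and 450/3 = 150. The range is 450 respondents per arm split into 3 to 5 groups, that is, 3 to 5 levels of one factor.

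**Power per arm.** Continuity-corrected: power = Φ{[d − 1/n − z_α √(2p̄(1 − p̄)/n)] / √[(p1(1 − p1) + p2(1 − p2))/n]}. For n = 90 at 0.1% vs 10% this is Φ[(0.0879 − 0.0640)/0.0318] = Φ(0.75) = 77%. The exact Fisher column was obtained by enumerating all outcomes.

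| n per arm | 0.1% vs 10%, corrected | 0.1% vs 10%, Fisher | 1% vs 10%, corrected | 1% vs 10%, Fisher |
|---|---|---|---|---|
| 90 | 77% | 88% | 64% | 70% |
| 95 | 80% | not run | 67% | not run |
| 112 | 87% | 96% | 76% | 83% |
| 121 | 90% | 98% | 80% | 86% |
| 150 | 96% | >99% | 89% | 94% |
| 450 | >99% | not run | >99% | not run |

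**The case against.** The best defence is that the error is harmless as printed. It overstates the need (121 against 95), and 450 per arm is ample at either rate. The section also supports its size on other grounds: the expected number of patients who would withhold consent or are undecided, and the comparison of preferences. All of this stands, and it confines the point to the stated n and the subgroup sentence.

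Several stronger readings are tempting, but the protocol does not support them.

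- **That 0.1% is a misprint for 1%.** This is a simple explanation, since it leaves the other stated settings alone. But two other single changes also give 121. The 0.1% is printed twice, and it fits the stated difference of at least 10 points better (9.9 points against 9).
- **That 90 to 150 is underpowered at the printed rates.** Mostly it is not. With the correction, only 90 to 94 falls below 80%, by less than 3 points, and exact Fisher power at 90 is 88%. The basic plan of analysis does not tie the analysis to a continuity-corrected test.
- **That 3 to 4 factors would be crossed.** Crossing two-level factors would leave 450/8 ≈ 56 to 450/16 ≈ 28 per arm per cell. The protocol's own gloss of 90 to 150 points instead to one factor at a time. The word factors is loose, and correcting it is enough.
- **That the blood-draw group was promised this power.** Study sample lists "surgery or biopsy (1600 patients) or blood drawing (200 patients"), but the power section makes no claim for the 200 by name.
- **That consent will be analysed only in questionnaire respondents.** Planning on 450 does not define the analysis set. The basic plan of analysis does not restrict it, and the SAP, which is not shown, may settle it.

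**Conclusion.** The sample size statement is wrong as written. The printed inputs give 95 per group, and the printed 121 is about 27% higher (121/95 = 1.27). At least one of the rate, the power, the alpha or the 121 must be wrong, and only the sponsor can say which.

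The subgroup sentence contradicts the 121, because 90 to 120 of its range lies below that figure. Whether this is a real shortfall depends on which number is the error. If 0.1% is right, the range is close to adequate throughout. If 1% is right, the 80% target is met only from 121 upwards by the corrected formula, and power at 90 is about 64%.

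The main consent comparison is not in doubt. These conclusions assume 1:1 comparisons, 450 respondents per arm split equally across levels, and the normal-approximation formula with continuity correction that the section names. Unequal levels would leave the smaller ones with less power than shown.

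**What to change.** 1. State which non-consent rate, power and alpha produced 121. Then correct either the n (95 for the inputs as printed) or the input that was misreported.
2. Replace the subgroup sentence with one that matches: one factor at a time, with 3 to 5 levels of about equal size, giving 450/5 = 90 to 450/3 = 150 respondents per arm per level. Give the continuity-corrected power: about 77% to 96% if the rate is 0.1%, or about 64% to 89% if it is 1%. Drop the reference to 3 to 4 factors.

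The cost is protocol wording only. No patients are added, and neither the arms nor the main comparison change. The downside is that the stated subgroup power may look less favourable than it does now.

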A disadvantage of the current opt-out procedure, however, is that patients are generally not aware that tissue is stored for a future diagnosis. This is an important deficit when considering the importance of stored tissue for an eventual future diagnosis of the patient or her/his relatives. The fact that patients are not aware of tissue storage also signals the fact that most patients are not aware that they can opt-out (declare that they do not agree to the use of their extracted and stored tissue in medical research). In our exploratory research (see below) we therefore devised and tested a procedure that ensures that patients are aware of storage and research with residual tissue. This procedure, opt-out plus, involves verbal information and a leaflet about tissue research. With this information the patient can consider opting-out. In contrast to informed consent, the opt-out plus procedure does not require much administrative work because there is no need to process consent forms from all patients. Moreover, the opt-out plus procedure may not lead to lower consent rates and bias in the available tissue, as is very likely the case with the informed consent procedure, because this procedure does not depend on an action taken by patients.

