## **Preliminary results**

Over the last years our research group has conducted three explorative studies about consent and patient information. We examined how patients in the NKI-AVL and VUmc with breast cancer, prostate cancer and colorectal cancer wished to be informed about research with stored tissue, and what kind of consent procedure they preferred. The studies showed that most respondents (96-98%) consented to research with their tissue. This is in line with other research. In the first study, patients were asked whether they preferred informed consent or opt-out. Most patients preferred a consent procedure with active information, but did not consider the signing of a consent form important, especially because they endorsed research and wanted to minimize bureaucratic burden. The respondents in these studies suggested a procedure that was labelled 'opt-out plus': patients receive verbal and written information, a special leaflet about tissue and research, and the option to opt-out.

In the two subsequent studies, the opinion of patients about the three consent procedures - informed consent, opt-out and opt-out plus- was explored by means of written questionnaires and telephone interviews. Further, the influence of these procedures on consent rates and availability of residual tissues for scientific research was studied. The majority of patients

preferred opt-out plus over the two other procedures. Opt-out and opt-out plus resulted in the highest availability of tissue for scientific research.

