## ***Basic plan of analysis***

Analysis will first be performed to evaluate the comparability of the intervention groups and the control group at study entry in terms of sociodemographic and clinical characteristics. Student's t-test or appropriate non-parametric statistics will be used, depending on the level of measurement. If the groups are found not to be comparable on one or more background variables, those variables will be employed routinely as covariates in subsequent analyses using multivariate models, such as logistic regression.

The proportion of the outcomes in each intervention arm, i.e. consent rates and patients' satisfaction with and preference for a consent procedure, the proportion of patients aware of storage of tissue and research use, and the satisfaction with and preference for a consent procedure of the medical staff, will be evaluated by comparison of the informed consent

versus the opt-out plus group, and the opt-out plus versus the opt-out group by non-parametric or parametric tests as appropriate. Patient characteristics, satisfaction with and preferences for the information and consent procedures will be evaluated according to patient characteristics such as age, educational level, sex, hospital type, type of clinical procedure, and disease type. All analyses will be performed using SPSS.

A qualitative analysis of the information needs and appreciation of the patients for the consent procedures will be evaluated through questions in the questionnaire and telephone interviews with a representative group of patients who completed the questionnaire.

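### One unsourced 0.1% non-consent rate is used for both opt-out arms, so the claim that subgroups of 90 to 150 are adequately powered is not established for informed consent versus opt-out plus

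*Protocol*

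**What the plan says.** The protocol's section on sample size and power sets out to show that "the two interventions result in a difference of at least 10% in consent rates" and uses "0.1% non-consent in the opt-out plus or opt-out group versus 10% in the informed consent group". From this it concludes that "121 patients per group are needed (80% power and a 2-sided alpha of 0.05; with continuity correction"). The only source offered is "The difference of 10% is based on our earlier research"; no rates by arm are reported.

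The same section raises recruitment to 600 per arm, or 450 at a 75% response. It says that subgroups of 90 to 150 per arm would then still be adequately powered for 0.1% against 10%.

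Two earlier figures bear on refusal. Under Preliminary results: "The studies showed that most respondents (96-98%) consented to research with their tissue". In the sample-size section: "4.6% of respondents indicated in the questionnaire that they wanted to withhold consent or that they did not know whether they wanted to". Neither is split by consent procedure.

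The basic plan of analysis compares informed consent "versus the opt-out plus group, and the opt-out plus versus the opt-out group by non-parametric or parametric tests as appropriate". It also evaluates results by hospital type, clinical procedure and disease type.

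**The concern.** The two opt-out arms share one rate but were built to differ. In the control arm patients get usual care and may come across a general hospital leaflet. The introduction says that under the current procedure "most patients are not aware that they can opt-out", so near-zero refusal is plausible there. In opt-out plus, staff tell each patient about research use and hand over a dedicated leaflet, an opt-out form and a stamped envelope. A rate of 1 in 1,000 may turn out to be right for that arm, but nothing in the protocol supports it.

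This matters because subgroup power is the stated reason for going well beyond 121 per group, and because informed consent versus opt-out plus is a planned comparison. If refusal in opt-out plus is a few per cent, a null result in one hospital type or setting would carry little information. The shared rate also assumes no difference between opt-out plus and opt-out, so the other planned comparison of consent rates has no sizing behind it.

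**Working it through.** **Inputs.** From the sample-size section: 0.1% and 10% non-consent, two-sided alpha 0.05, 80% power, continuity correction, 450 analysable per arm, 90-150 per subgroup. Assumed here: opt-out plus non-consent of 0.1% to 4%. The upper end comes from the 96-98% who consented in earlier studies.

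**Formulas.** With difference d, mean rate p̄ and q = 1 − p:
- n₀ = [1.96·√(2p̄q̄) + 0.842·√(p₁q₁ + p₂q₂)]² / d²
- with correction, n = (n₀/4)·[1 + √(1 + 4/(n₀d))]²
- power at n = Φ{[d − 1/n − 1.96·√(2p̄q̄/n)] / √((p₁q₁ + p₂q₂)/n)}

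**1. The plan's own figure.** For 0.1% v 10%: d = 0.099, p̄ = 0.0505, √(2p̄q̄) = 0.3097, √(p₁q₁ + p₂q₂) = 0.3017. Then n₀ = (0.6070 + 0.2539)²/0.009801 = 75.6, and with correction n = 94.7, so 95 per group. The printed 121 does not follow from the printed inputs. It does follow from 1% v 10% at 80% power (120.7), from 0.1% v 10% at 90% power (120.1), or from 0.1% v 10% at alpha 0.05/3 and 80% power (120.4). The document states none of these.

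**2. Subgroup power against 10% in informed consent.** Two worked cases at n = 90:
- 0.1%: (0.0879 − 0.0640)/0.0318 = 0.75, power 77%.
- 2%: (0.0689 − 0.0694)/0.0349 = −0.01, power 49%.

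| Opt-out plus rate | n for 80% power | Power at 90 | Power at 150 | Power at 450 |
|---|---|---|---|---|
| 0.1% | 95 | 77% | 96% | >99% |
| 1% | 121 | 64% | 89% | >99% |
| 2% | 162 | 49% | 77% | 99.9% |
| 3% | 222 | 36% | 61% | 99% |
| 4% | 316 | 25% | 44% | 93% |

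Without the correction, power at 90 is 87%, 76%, 62%, 48% and 35% down the table, and at 150 it is 98%, 93%, 83%, 69% and 53%.

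**3. Keeping a 10-point difference.** If informed consent non-consent rises along with opt-out plus:

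| Rates | n for 80% power | Power at 90 | Power at 150 |
|---|---|---|---|
| 2% v 12% | 121 | 65% | 89% |
| 3% v 13% | 134 | 60% | 85% |
| 4% v 14% | 147 | 55% | 81% |

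**4. Larger denominator.** If consent can be counted for all 600 randomised per arm (an assumption), the same subgroups hold 120-200. Against 10%, power at 200 is 89%, 75% and 58% for 2%, 3% and 4%.

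**5. Opt-out plus versus opt-out.** For 2% v 0.1%, power is 70% at 450 per group and 84% at 600.

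**The case against.** **The earlier figures are not opt-out plus rates.** They pool respondents over studies and procedures, and the 4.6% includes people who did not know. In opt-out plus, silence counts as consent and refusal takes a posted form, so the recorded rate may be well below stated unwillingness. This stands. A reader might infer that the plan's own data put opt-out plus refusal at 2-4%; the documents do not say so, and 2-4% is only the upper part of a plausible range.

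**Grouping the opt-out arms is reasoned.** The hypotheses expect both to have the highest consent rates, the introduction argues that opt-out plus may not lower consent, and the earlier studies found tissue availability highest under both. That supports similar rates, but not the value 0.1%.

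**The difference may be preserved.** Patients who would refuse are also present in the informed consent arm, where unreturned forms add to non-consent. With 10 points kept, 150 per group is enough. This stands too, so a reader who infers that subgroup power is simply absent, or that it is 25-77% as a fact, goes too far.

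**The expected counts do not contradict each other.** One might set the predicted 62 patients (0.046 × 1350) against the 46 implied by the sizing rates (0.001 × 900 + 0.10 × 450). The first counts people who want to withhold consent or are unsure; the second counts consent not obtained, which under informed consent can include unreturned forms. They need not agree.

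**The decision rule is not written for subgroups.** The Outcomes section requires consent rates at least as high as in the other procedures, but does not apply this within subgroups. Misreading a null subgroup result is a risk, not something the plan prescribes.

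**Conclusion.** The point holds as a statement about power that has not been shown. At 90 per subgroup, power under the plan's own continuity-corrected convention is below 80% at every rate from 0.1% to 4%, and is 55-65% if a 10-point difference is kept; 90 is also below the plan's own 121. Without the correction, 90 would suffice at 0.1% (87%) but not at 1% or above. At 150 per subgroup, power is adequate up to about 1-2%, falls to 44% at 4% v 10%, and is 81-89% with a 10-point difference.

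The main comparison of informed consent with opt-out plus is not threatened: it keeps about 93% or more at 450 per group across the range. The conclusion rests on two assumptions that the documents cannot settle: the true opt-out plus rate, and whether informed consent stays at 10% or moves with it. The 0.1% may itself be a slip for 1%, since 1% v 10% gives 121, but other combinations give that number as well.

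**What to change.** Revise the sample-size section as follows:

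- Give separate assumed non-consent rates for opt-out and opt-out plus, labelled as assumptions, with a source where one exists.
- Reconcile the inputs with the result: 0.1% v 10% at 80% power gives 95 per group. If 121 is intended, state the rates, power or alpha that produce it.
- Replace the statement that subgroups of 90 to 150 are adequately powered with a short table of power over 0.1-4% for opt-out plus, showing both a fixed 10% and a fixed 10-point difference.
- Report subgroup contrasts of opt-out plus with informed consent as estimates with confidence intervals.
- State that the whole-arm contrast keeps about 93% or more at 450 per group.
- Add the power for opt-out plus versus opt-out, for example about 70% for 2% v 0.1% at 450 per group.

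The cost is rewording only. No extra patients are needed; the downside is a less favourable stated subgroup power.

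### The 121 per group for consent rates does not follow from its stated inputs, which give 95, and the subgroup floor of 90 lies below both figures

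*Protocol*

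**What the plan says.** The section Sample size, statistical power sets out to detect "a difference of at least 10% in consent rates" and gives the calculation as "0.1% non-consent in the opt-out plus or opt-out group versus 10% in the informed consent group, 121 patients per group are needed", with "80% power and a 2-sided alpha of 0.05; with continuity correction". Allocation is equal: "The study sample will be composed of 1800 patients, evenly distributed over the three study arms" (Study sample).

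The section then argues for up to 600 patients per arm so that subgroups can be analysed and adjustment factors included. It starts from the expected questionnaire respondents, "with a response rate of 75% and hence with 450 participants per group", and says "we could stratify for 3 to 4 factors, i.e. 90-150 per subgroup". It concludes that this leaves "90-150 per subgroup, and still have enough power to investigate a difference in response rate of 0.1% versus 10" per cent. That sentence says response rate where the earlier one says non-consent. Because the two percentages are identical, I read both as the same contrast.

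**The concern.** Every input to the sample-size formula is printed, so the figure of 121 can be checked directly, and it does not come out. The paragraph also sets two standards for one contrast: 121 per group needed, then 90 per group enough. No formula is needed to see that conflict.

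Consent rate is one of the listed primary outcomes (Study objectives), and it decides which procedure serves research best (Outcomes). This is the only calculation given for it. It also carries the claim that consent can be compared within subgroups, and Study objectives commits to such comparisons by disease severity, clinical procedure, diagnosis, hospital type and demographics. If the planning rate was really 1%, the smaller subgroups in the stated range are underpowered. If it was 0.1%, both the required size and the power that 121 delivers are mis-stated. Either way, a reader cannot tell which subgroup sizes are adequate.

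**Working it through.** **Inputs** (all from the Protocol): non-consent p1 = 0.001 (opt-out plus or opt-out) and p2 = 0.10 (informed consent); two-sided alpha 0.05, z = 1.960; power 80%, z = 0.8416; equal allocation; continuity correction. Respondents per arm: 0.75 × 600 = 450. Subgroup sizes: 90 to 150 per arm, that is 450/5 to 450/3.

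**Formula** (standard two-proportion formula with pooled variance under the null, then the Fleiss correction), with d = p2 − p1 and p̄ = (p1 + p2)/2:

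- n = [z_α √(2p̄(1−p̄)) + z_β √(p1(1−p1) + p2(1−p2))]² / d²
- n_cc = (n/4) × [1 + √(1 + 4/(n·d))]²

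**Step 1: the printed inputs.** d = 0.099 and p̄ = 0.0505.

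- n = (1.960 × 0.3097 + 0.8416 × 0.3017)² / 0.099² = (0.6070 + 0.2539)² / 0.009801 = 75.6
- n_cc = (75.6/4) × (1 + 1.2387)² = 94.7, so **95 per group**

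The printed 121 is 26 higher, or 27% above 95.

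**Step 2: is it a different formula?** With the same rates, 80% power and alpha 0.05:

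| Variant | Per group |
|---|---|
| No continuity correction | 76 |
| One-sided, corrected | 79 |
| Unpooled variance, corrected | 92 |
| Fully pooled variance, corrected | 96 |
| Arcsine | 47 |
| Fisher's exact test | about 80 |
| 95 inflated for 75% response (95/0.75) | 127 |

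None gives 121.

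**Step 3: which inputs do give 121?**

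- 1% versus 10%, 80% power: n = 99.5, n_cc = 120.7, so 121.
- 0.1% versus 10%, 90% power: n = 100.7, n_cc = 120.1, so 121.
- 0.1% versus 10%, 80% power, alpha 0.05/3: n_cc = 120.4, so 121. The section prints alpha 0.05, so this does not rescue the figure, but it is a third possible source.

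**Step 4: power at the subgroup sizes.** Inverting the same formula, power = Φ{[(d − 1/n) − z_α √(2p̄(1−p̄)/n)] / √([p1(1−p1) + p2(1−p2)]/n)}. Fisher's exact power, by enumeration, is in brackets.

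| n per arm | 0.1% v 10% | 1% v 10% |
|---|---|---|
| 90 (450/5) | 77% (88%) | 64% (70%) |
| 112 (about 450/4) | 87% (96%) | 76% (83%) |
| 121 | 90% (98%) | 80% (86%) |
| 150 (450/3) | 96% (>99%) | 89% (94%) |

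By the stated method, 90 per arm misses 80% on either reading. If 1% was meant, every size below 121 misses it, which is the lower half of the 90 to 150 range.

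**Step 5: the protocol's own standard.** 450/121 = 3.7, so 450 respondents per arm can be split into at most three equal subgroups that each meet 121. The floor of 90 corresponds to five.

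**The case against.** The best defence is that the slip does little harm.

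- **The error is conservative if the printed rates are right.** 121 exceeds 95, and 450 respondents per arm give ample power for the whole-arm comparison on any reading. No recruitment target or decision rule depends on 121. This stands, and it limits the weight of the point.
- **The subgroup claim is then nearly true.** At 90 per arm, power is 77% with correction, 86% without and 88% by Fisher's exact test. The subgroup sentence names no threshold, and the section accepts 75% power for the preference outcome. This stands for the 0.1% reading. If 121 is replaced by 95, the remaining shortfall is 90 against 95.
- **The 1% reading is conjecture.** The protocol prints 0.1% twice, and a gap of 9.9 points fits the stated 10% better than 9 points does. That is fair, although the same section also describes 43% versus 34%, a 9-point gap, as at least 10%. The document cannot settle the matter.
- **The size of 600 per arm has other grounds:** adjustment factors, about 62 non-consenting or undecided respondents, and the preference and satisfaction comparisons. This is correct; subgroup power is a main reason, not the only one. Five subgroups is also my inference from 450/90, since the text speaks of 3 to 4 factors.
- **Consent might be counted on all 600 per arm,** because the forms are returned separately from the questionnaire. Fifths would then be 120, practically 121. But the section itself works from 450.

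None of this makes 121 follow from its inputs, or removes the conflict between 121 needed and 90 enough as the paragraph stands.

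**Conclusion.** The concern holds. With the printed inputs the required size is 95 per group, and 121 cannot be reproduced by any variant tried at those rates, that power and that alpha. At least one of the rate, the power, the alpha or the result is wrong. On the printed rates, 121 gives 90% power by the stated method, not 80%.

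The subgroup statement is unsupported at its lower end: 77% power at 90 per arm under 0.1% versus 10%, and 64% under 1% versus 10%. The first is a small shortfall that an exact test would remove (88%). The second is material and remains with an exact test (70%).

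These figures assume equal subgroups, equal allocation within them, and 450 respondents per arm as the base. The whole-arm comparison is unaffected. This is an error that should be corrected in the justification and the subgroup claim; it does not undermine the trial's main comparison.

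**What to change.** Go back to the original calculation, establish which input was intended, and restate the paragraph accordingly:

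- **0.1% at 80% power:** replace 121 by 95, and say that 90 per arm gives about 77% power with continuity correction (88% by Fisher's exact test).
- **1% at 80% power:** change 0.1% to 1% in both places and keep 121. Raise the subgroup floor to 121, which means at most three equal subgroups of 150, and state that 90 would give about 64%.
- **0.1% at 90% power:** print 90%, keep 121, and state the lower power (77%) at 90.
- **An alpha adjusted for three comparisons:** print that alpha, and recompute the subgroup power with it.

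In each case, replace the general assurance about 90 to 150 with the power at 90, 112 and 150 per arm. Say whether the base is the 450 respondents or all 600 randomised, and use non-consent rather than response rate if that is what is meant.

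The cost is a sentence or two in one section. Enrolment and design stay as they are; under the 1% reading the protocol would claim fewer adequately powered subgroups.
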